#### **5.4 Subject Enrolment Log**

Investigators must keep a list of all subjects who are considered for enrolment into the study even if they are not subsequently enrolled. The subjects will be listed on a Subject Pre-Screening- / Screening Log. This log will list whether subjects were enrolled or not. If a subject is not enrolled, the main reason will be listed. The list will be prepared according to GDPR.

#### **5.5 Subject Identification List**

The investigator must also keep a confidential Subject Identification List of all subjects entered to treatment linking the subject's identifier (PatientID) to each subject's full identity to enable quality control of data and allow the Investigator to quickly identify a subject when needed. The list is kept by the investigator and must not be copied or retained by SelectImmune Pharma or KKS.

#### **5.6 Discontinuation Criteria**

##### **5.6.1 Withdrawal of patients from study treatment**

All subjects have the right to withdraw from the study at any time, for any reason, and without penalty or loss of benefits to which the patient is otherwise entitled. If the patient chooses to withdraw, the investigator must be informed immediately.

Treatment with study medication may also be terminated by the investigator for several reasons e.g.

- Any signs and symptoms considered by the investigator to be a safety issue
- Emergence of an unacceptable SAE/AE
- Any reason if it is in the best interest of the patient
- If the patient does not comply with investigational requirements.

Study treatment must be terminated for one of the following reasons:

- Withdrawal of patient's consent to study treatment
- Pregnancy
- Any other development in the patient's medical condition that has an unfavorable effect on the risk-benefit assessment for this individual as determined by the investigator.

If the investigator terminates the treatment with study medication prematurely, further medical treatment will be decided individually between the investigator and the patient.

In case of premature stop of study medication or the whole study for a patient by the investigator, the investigator has to inform the patient about his decision and has to record the primary reason for termination in the patient file and in the e-CRF. Final study evaluations will be done according to the visit schedule of the study. All data before termination may be used for final analysis.

### **5.6.2 Premature discontinuation of the study**

SelectImmune Pharma, the investigator, the IRB/IECs or competent authorities may decide to stop the trial, part of the trial or a trial site at any time. Procedures to be followed must be agreed.

If a trial is suspended or prematurely terminated, the investigator must inform the subjects promptly and ensure appropriate therapy and follow-up. As specified by applicable regulatory requirements, either the investigator or SelectImmune Pharma must promptly inform IRB/IECs and provide a detailed written explanation. Relevant competent authorities must be informed.

The trial must be terminated if the perception of the benefit/risk ratio (judged from clinical signs and symptoms, (S)AEs and/or remarkable safety laboratory changes) becomes unfavourable for the continuation of the trial.

Possible reasons for termination of the study could be but are not limited to:

- Unexpected accumulation of SAE/AE
- Major failure to adhere to the study protocol
- Inaccurate or incomplete enrolment or data collection

## **6 Trial Schedule and Assessments**

### **6.1 Schedule of Trial Procedures**

**Study chart (examples)**

|                                                                                                     | Screening
Visit 1 | Visits
2 and 5 | Visits
3 and 4                | Visit
6       | Safety Phone
Call | Visit
7 *      | Unscheduled visits |
|-----------------------------------------------------------------------------------------------------|----------------------|-------------------|----------------------------------|------------------|----------------------|-------------------|--------------------|
| Day                                                                                                 | Day
1             | Day
2 and 5    | Day
3 and 4                   | Day
15±2 days | Day 30               | Week
26±5 days |                    |
| Patients                                                                                            | All patients         | All patients      | Only patients of
Kineret® Arm | All patients     | All patients         | All patients      | All patients       |
| Visit window                                                                                        |                      |                   |                                  |                  |                      |                   |                    |
| Informed consent                                                                                    | X                    |                   |                                  |                  |                      |                   |                    |
| Subject demographics                                                                                | X                    |                   |                                  |                  |                      |                   |                    |
| In-/exclusion criteria                                                                              | X                    |                   |                                  |                  |                      |                   |                    |
| Anamnestic exclusion of
patients with active
severe infections, history
of viral hepatitis | X                    |                   |                                  |                  |                      |                   |                    |
| Anamnestic assessment
of tuberculosis history or
active tuberculosis                          | X                    |                   |                                  |                  |                      |                   |                    |
| Urine Pregnancy test                                                                                | X                    |                   |                                  |                  |                      | X                 |                    |
| Medical history and
concurrent diagnosis.                                                        | X                    |                   |                                  |                  |                      |                   |                    |
| Concomitant medication                                                                              | X                    | X                 | X                                | X                | X                    | X                 | X                  |
| Physical examination                                                                                | X                    |                   |                                  |                  |                      | X                 |                    |
| Randomisation                                                                                       | X                    |                   |                                  |                  |                      |                   |                    |

|                                                                                                  | Screening
Visit 1 | Visits
2 and 5 | Visits
3 and 4                      | Visit
6                 | Safety Phone
Call | Visit
7 *               | Unscheduled visits |
|--------------------------------------------------------------------------------------------------|----------------------|-------------------|----------------------------------------|----------------------------|----------------------|----------------------------|--------------------|
| Day                                                                                              | Day
1             | Day
2 and 5    | Day
3 and 4                         | Day
15±2 days           | Day 30               | Week
26±5 days          |                    |
| Patients                                                                                         | All patients         | All patients      | Only patients of
Kineret® Arm       | All patients               | All patients         | All patients               | All patients       |
| Dispensing of Study
Medication (Patient
randomised to Kineret®)                            | X                    | X                 | X                                      |                            |                      |                            |                    |
| Dispensing of study
medication
(Patient randomised to
Nitrofurantoin Uro-
Tablinen®) | X                    |                   |                                        |                            |                      |                            |                    |
| Adverse Event(s)                                                                                 | X                    | X                 | X                                      | X                          | X                    | X                          | X                  |
| Vital signs                                                                                      | X                    | X                 | X                                      | X                          |                      | X                          | X                  |
| Blood sample
(haematology)                                                                    | X                    | X                 | On Visit 3: only
WBC & differential | Only WBC &
differential |                      | Only WBC &
differential | X                  |
| Blood sample
(biochemistry)                                                                   | X                    | X                 |                                        |                            |                      |                            | X                  |
| Urine RNA                                                                                        | X                    | X                 |                                        | X                          |                      | X                          | X                  |
| Urine Proteomics                                                                                 | X                    | X                 |                                        | X                          |                      | X                          | X                  |
| Urine analysis culture (dip
slide, bacterial culture)                                         | X                    | X                 | X                                      | X                          |                      | X                          | X                  |

|                      | Screening
Visit 1 | Visits
2 and 5 | Visits
3 and 4                | Visit
6       | Safety Phone
Call | Visit
7 *      | Unscheduled visits |
|----------------------|----------------------|-------------------|----------------------------------|------------------|----------------------|-------------------|--------------------|
| Day           | Day
1             | Day
2 and 5    | Day
3 and 4                   | Day
15±2 days | Day 30               | Week
26±5 days |                    |
| Patients      | All patients         | All patients      | Only patients of
Kineret® Arm | All patients     | All patients         | All patients      | All patients       |
| Blood sample (RNA)   | X                    | X                 |                                  | X                |                      | X                 | X                  |
| Blood sample (DNA)   | X                    |                   |                                  |                  |                      |                   |                    |
| Urine Flow Cytometry | X                    | X                 |                                  | X                |                      | X                 | X                  |
| ACSS                 | X                    | X (on day 5)      |                                  | X                | X                    | X                 | X                  |

\* Final visit including Early Termination Visit (see below).

## 6.2 Description of Trial Visits

All procedures and assessments to be performed at each visit are detailed below and in the above study chart. All data will be recorded in the Patient's hospital notes or in a worksheet, as appropriate and be reported in the eCRF.

### Day 1

The subject will be considered for enrolment in the study, based on a diagnosis of cystitis. The investigator will explain the nature, purpose and risks of the trial and provide the subject with a copy of the Patient Information and Informed Consent. The patient will be asked to consider and evaluate participation in the study in accordance with the Helsinki Declaration and the local applicable laws. This visit is planned for all subjects independent of treatment arm.

#### Visit 1 Screening and Randomisation

- Patient Consent collected
- Demographics
- Final check for study eligibility
- Anamnestic exclusion of patients with active severe infections, history of viral hepatitis
- Anamnestic assessment of tuberculosis history or active tuberculosis
- Urine Pregnancy test
- Medical History and concurrent diagnosis
- Concurrent Medical Conditions
- Concomitant Medication
- Physical Examination
- Randomisation
- Dispensing of Kineret® (to patients randomised to Kineret®)
- Patient supplied with Nitrofurantoin Uro-Tablinen® for 5 days treatment and instructed how to take the drug to fully comply with the dosage recommendation
- Adverse Events
- Vital signs
- Blood Samples (Haematology and Biochemistry) including WBC and differential for monitoring of neutrophils granulocytes
- Urine analysis RNA
- Proteomics
- Urine analysis dip slide and bacterial culture
- Blood sample (RNA)

- Blood sample (DNA)
- Flow Cytometry urine sample
- ACSS

#### Visits 2 and 5 Treatment Visits

Applicable to study patients of both treatment arms.

- Concomitant Medication
- Dispensing of Kineret®
- Adverse Events
- Vital Signs
- Blood sample (haematology and biochemistry)
- Urine analysis (RNA)
- Proteomics
- Urine analysis dip slide and bacterial culture
- Blood sample (RNA)
- Flow Cytometry urine sample
- ACSS (only on visit 5)

#### Visits 3 and 4 Treatment Visits

Only applicable to study patients randomised to Kineret® treatment.

- Concomitant Medication
- Dispensing of Kineret®
- Adverse Events
- Vital Signs
- Blood sample for assessment WBC and differential for monitoring of neutrophils granulocytes (only on day 3)
- Urine analysis bacterial culture

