#### 3.2.2 Safety Endpoints

Change in laboratory safety variables, vital signs, physical examination from baseline and the incidence of adverse events, treatment emergent adverse events, serious adverse events during the trial.

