#### 3.2.3 Secondary Endpoints

- a) Presence of bacteriuria at each visit up to week 26 of study
- b) Presence of leucocyturia at each visit up to week 26 of study
- c) Recurrent UTI episodes up to 6 months
- d) Urine proteomics
- e) Gene expression analysis
- f) DNA sequence analysis

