## 9.3 Statistical Analysis

The statistical analysis will be specified in a Statistical Analysis Plan prior to Database lock. All data analysis will be based on statistical hypothesis testing. Population variables, adverse events and efficacy variables will be formally evaluated. The primary objective of the trial is to evaluate the safety and efficacy of Anakinra treatment for episodes of acute cystitis in patients with recurrent disease. No formal sample size calculation evaluating the power of the trial has been performed. However, a consideration regarding the sample size was made based on previous studies of Anakinra in a murine acute cystitis model. For efficacy, the sample size was based on analysis of symptom scores, inflammatory parameters and bacterial cultures. A sample size of 20 patients in the Anakinra treatment group and ten in the group receiving antibiotics was deemed suitable to achieve criterion for significance (alpha) 0.05 and power 90% using the paired samples 1-tailed t-test. The null hypothesis is H0: mean change in symptom score = 0 and the alternative hypothesis is HA: mean change in symptom score > 0.

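### On Days 3 and 4 only Kineret patients are scheduled for adverse-event questioning and safety checks, so transient adverse events may be recorded more often in that arm

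*Protocol*

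**What the plan says.** The schedule in protocol section 6.1 marks Days 3 and 4 as "Only patients of Kineret® Arm". Section 6.2 repeats the restriction for Visits 3 and 4: "Only applicable to study patients randomised to Kineret® treatment". The procedures listed there are concomitant medication, AEs, vital signs, "Urine analysis bacterial culture" and, on Day 3, a white-cell count with differential to monitor neutrophils. Visits 2 and 5, by contrast, are "Applicable to study patients of both treatment arms", and both include AE questioning and culture.

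The safety endpoints in section 3.2.2 include "the incidence of adverse events, treatment emergent adverse events, serious adverse events during the trial". Section 9.3 says: "Population variables, adverse events and efficacy variables will be formally evaluated". It writes out no between-arm AE test. One is implied, because the same section bases all data analysis on hypothesis testing and section 3 sets Kineret against nitrofurantoin. The bacteriuria endpoint in section 3.2.3 is "Presence of bacteriuria at each visit up to week 26 of study", and section 9.3.2 tabulates by-visit data on observed cases.

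**The concern.** Section 2.5.1 says that AEs are gathered partly by spontaneous report and partly by staff at regular visits. The number of visits therefore affects how many events are recorded, and during treatment it differs by arm. A short-lived headache or nausea on Day 3 is asked about the same day in one arm and not until Day 5 in the other.

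Objective findings raise a second issue. Appendix 1 requires any laboratory abnormality judged clinically significant to be recorded as an AE, and section 6.4 grades abnormal vital signs by clinical significance. Section 8 lists neutropenia as a Kineret reaction and blood-count changes as a nitrofurantoin reaction. A transient Day 3 fall in neutrophils could become an AE on Kineret, but on nitrofurantoin no scheduled test would reveal it. Recall does not help there. At stake is whether a difference in AE incidence between 20 and 10 patients can be read as a drug effect.

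**Working it through.** The protocol gives no figure to reproduce here. The contact counts come from the documents; the daily risks, recall shares and per-test chances below are assumptions.

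**Counts (sections 6.1 and 6.2)**

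| Scheduled item | Kineret | Nitrofurantoin |
|---|---|---|
| AE enquiries, Days 2–5 | 4 (Days 2, 3, 4, 5) | 2 (Days 2, 5) |
| AE enquiries after first dose to Day 30 | 6 (adding Visit 6 and the Day 30 call) | 4 |
| White-cell count and differential, Days 2–5 | 3 (Days 2, 3, 5) | 2 (Days 2, 5) |
| Post-baseline cultures to week 26 | 6 | 4 |
| Symptom score during treatment | Days 1, 5 | Days 1, 5 |

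**Symptomatic AEs.** Let q be the same true daily risk of a transient AE in both arms on each of Days 2–5, and r the share of Day 3–4 events that nitrofurantoin patients still report by Day 5. Assume full capture on Kineret.

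- Kineret recorded incidence: 1 − (1 − q)^4
- Nitrofurantoin recorded incidence: 1 − (1 − q)^2 × (1 − rq)^2

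With q = 0.10, Kineret is 1 − 0.9^4 = 34.4%. For nitrofurantoin:

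- r = 1: 34.4%, gap 0
- r = 0.8: 1 − 0.81 × 0.92^2 = 31.4%, gap 2.9 points (about 3)
- r = 0.5: 1 − 0.81 × 0.95^2 = 26.9%, gap 7.5 points
- r = 0: 1 − 0.81 = 19.0%, gap 15.4 points. This is a mathematical limit, not an expected case.

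For events arising on Days 3–4 alone, the apparent Kineret-to-nitrofurantoin ratio is 1/r: 1.25 at r = 0.8 and 2.0 at r = 0.5.

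**Blood-count AEs.** Let p be the chance that one test shows a transient abnormality recorded as an AE, the same in both arms and independent between days. The chance of at least one on Days 2–5 is 1 − (1 − p)^3 versus 1 − (1 − p)^2.

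- p = 0.02: 5.9% v 4.0%
- p = 0.05: 14.3% v 9.8%
- p = 0.10: 27.1% v 19.0%

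An abnormality that persists to Day 5 is seen in both arms, so persistence shrinks these gaps.

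**Bacteriuria.** It is defined and tabulated visit by visit. At each shared visit (Days 1, 2, 5, Visits 6 and 7) both arms have the same culture, so equal true rates give no schedule-induced difference. On Days 3 and 4 there is no scheduled control culture and nothing to compare. Bias would arise only if visits were pooled. Any positive post-baseline culture, at an assumed 20% per visit with independent visits, would be 1 − 0.8^6 = 74% v 1 − 0.8^4 = 59%. The protocol specifies no such pooled measure.

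**The case against.** The asymmetry follows from the treatments: Kineret is injected at the clinic each day and nitrofurantoin is taken at home. In an open-label pilot, watching the experimental arm more closely is defensible. Any distortion would probably make Kineret look worse, not falsely safe. All of this stands, but none of it requires leaving control patients unasked on two days.

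A reader might infer that AEs from Days 3 and 4 are recorded in one arm only, and that Kineret will therefore show an excess of about 15 points. The documents do not support that. Nitrofurantoin patients are asked on Day 5, one or two days later, and again at Visit 6 and Day 30. Section 6.2 (Unscheduled Visits) and section 6.10.5 tell patients in both arms to contact the site about side effects or AEs. Section 7.1 requires recording for 30 days after the last dose in both arms. The 15-point figure needs all of these routes to fail. With 10 control patients, one patient is 10 points, so even the 7.5-point gap is less than one patient.

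A reader might also infer that the bacteriuria comparison or the primary endpoint is biased. Neither is: shared visits compare like with like, and the symptom score is taken on Days 1 and 5 in both arms. Section 9.3.1 already fixes the laboratory summaries and shift tables at Visits 6 and 7, so the Day 3 blood count affects the comparison only through AEs.

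Finally, the statistical analysis plan, which is not shown, may name the visits used for comparison. It could not supply Day 3–4 observations that were never collected from controls.

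**Conclusion.** The concern holds as a risk of differential ascertainment, limited to transient AEs and to AEs triggered by the Kineret-only Day 3 blood count or Day 3–4 vital signs. The likely direction is more recorded AEs on Kineret. Its size cannot be derived from the protocol, which gives neither AE rates nor recall. For symptoms it is zero with full recall at Day 5, and about 3 to 7.5 points at 80% to 50% recall under an assumed 10% daily risk. For test-triggered AEs it does not depend on recall, but shrinks if the finding persists to Day 5. The consequence also rests on reading section 9.3 as implying a between-arm AE comparison. This is a cheap improvement to the safety comparison; it does not threaten the primary result.

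**What to change.** In sections 6.1 and 6.2, add a scripted telephone contact on Days 3 and 4 for the nitrofurantoin arm. It should ask the same AE and concomitant-medication questions as the Kineret visits and be modelled on the existing Day 30 safety call. In section 9.3, add that:

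- for the between-arm AE comparison, AEs identified only from Day 3–4 laboratory or vital-sign findings in the Kineret arm are listed separately;
- any pooled urine or vital-sign comparison uses shared visits only.

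The cost is about 20 short calls (10 patients × 2 days) by existing staff and a few sentences of text. Telephone questioning is slightly weaker than a visit, so the imbalance is reduced rather than removed. If enrolment has ended, the two analysis statements can still be adopted, with the unequal AE enquiry reported as a limitation.
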